**Effectiveness**					
% PLWH w/diagnosed HTN receiving anti-HTN medication with controlled BP	19%	64%	45%	> 99%	21%
**Adoption**					
% PLWH w/HTN prescribed anti-hypertensive medications	57%	80%	23%	93%	22%
% PLWH w/HTN with waist and hip circumference recorded in the EHR	0%	50%	50%	> 99%	10%
% PLWH w/HTN with 10-year CVD risk calculated in the EHR	2%	20%	18%	98%	13%

All power calculations were conducted using formulae appropriate for a pair-matched cluster randomized trial [21].

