## Interventions

### Explanation for the choice of comparators {6b}

(i)*Active comparator/treatment arm*: Our treatment arm will be composed of clinics with interventions for integrating hypertension and cardiovascular diseases care (InterCARE), namely, provider training on HTN/CVD, the use of adapted electronic health record (EHR)—especially electronic reminders, and use of treatment partners for PLWHIV with hypertension.(ii)*Placebo comparator/control arm*: Given our set of interventions as the treatment arm, the control arm will be composed of clinics without integrated care of HIV and hypertension. Care in these clinics is as usual, with no EHR modifications and no organized-updated training of health care workers on hypertension management. Thus, their training would have been at nursing/medical school or at some point in the past. Enrolled participants also do not have designated treatment partners. With this placebo comparator, hypertension is managed by a provider using any guidelines of their choosing.

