### Strategies to improve adherence to interventions {11c}

We believe that our EHR modifications to include prompts for recording anthropometry, cardiovascular disease risk factors, and blood pressure, among others, facilitate adherence to our intervention protocols. Furthermore, we have planned 6-monthly refresher trainings and retraining in sites where the staff turnover exceeds 50%. Pairing of patients with treatment partners will facilitate communication between them to support medication and lifestyle adherence as well as attendance of clinic appointments. We will also have patient/treatment partner booster sessions conducted via telephone: for patients with controlled BP, booster calls will take place about 3 months after initial clinic training session; for patients with uncontrolled BP, booster calls will take place on a monthly basis after initial clinic training, until BP is controlled.

Our DCF includes a question on self-reported medication adherence, we however do not directly monitor drug levels for adherence.

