### Sample size {14}

The InterCARE trial aims to recruit a total of 4652 PLWH with HTN across the intervention and control sites and up to 2326 treatments partners. Assuming unequal numbers of randomized controlled trial (RCT) enrollees per clinic, a within-clinic correlation of 0.055 [20], 10% refusal rate, 10% loss to follow-up at 12 months, a two-sided 95% confidence interval, and independent co-primary outcomes, we will need to enroll approximately 333 PLWH with hypertension on average per clinic from 14 clinics (Table 2). The number of participants to be enrolled per clinic assumes a 25% prevalence of hypertension [20] and will vary based on clinic volume. This sample size will provide > 90% power to detect achievement of intervention arm targets for all quantitative outcomes assessed within the RE-AIM framework. Of note, for all quantitative endpoint, we will have adequate power to detect smaller, yet still clinically relevant, intervention effect sizes.

**Table 2 Tab2:** Power calculations based on selected RE-AIM measures

	Proportion at study end				
Endpoint	Standard of care	Intervention targets	Absolute difference	Power to reach intervention targets	Minimum detectable difference with 90% power

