## Statistical methods

### Statistical methods for primary and secondary outcomes {20a}

Primary analyses will be based on the intention-to-treat principle supported by per protocol analysis. The primary effectiveness outcome will be analyzed using a generalized linear mixed model (GLMM). The model will have a binomial distribution and log link function with the treatment (treatment vs control) as fixed effect, clusters, and pairs as random effects. From GLMM, the risk ratio with 95% confidence intervals (CI) will be calculated.

In addition, adjusted GLMM model analysis will be performed with covariates measured at baseline being added into the above GLMM model. The following variables will be considered in the covariate adjusted analysis: age, sex, education, level of income, waist to hip ratios (or body mass index (BMI)), physical activity (estimated number of minutes walked per week), smoking, and alcohol consumption.

Analysis of secondary binary outcomes will be analyzed similarly as the analysis of primary outcome using GLMM models. Analysis of secondary continuous outcomes will be performed using GLMM models with normal distribution and identity link function. The models will have the treatment as fixed effect, cluster, and pair as random effects. The mean differences with 95%CIs between treatment and control will be derived from the GLMM model.

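### The waist/hip-recording endpoint is planned at 0% in control clinics, where the risk ratio named in {20a} has no finite estimate; the >99% power belongs to a risk-difference analysis

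*Protocol article*

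**What the plan says.** - **Planning values.** The Adoption block of Table 2 (Sample size {14}) lists "PLWH w/HTN with waist and hip circumference recorded in the EHR" at 0% standard of care, 50% target, absolute difference 50%, power >99%, and a minimum detectable difference of 10% at 90% power. The table note bases all power figures on formulae for a pair-matched cluster randomized trial.
- **Control EHR.** On comparators, {6b} says of the control arm: "Care in these clinics is as usual, with no EHR modifications". In {11c} the intervention side is described as having "our EHR modifications to include prompts for recording anthropometry, cardiovascular disease risk factors, and blood pressure, among others".
- **Model.** In {20a} the primary effectiveness model is set out: "The model will have a binomial distribution and log link function with the treatment (treatment vs control) as fixed effect", with clusters and pairs as random effects. The effect measure follows: "From GLMM, the risk ratio with 95% confidence intervals (CI) will be calculated". It is then extended: "Analysis of secondary binary outcomes will be analyzed similarly as the analysis of primary outcome using GLMM models". No other effect measure is named for a binary outcome.

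**The concern.** A risk ratio divides by the control proportion. For this row the plan itself expects that proportion to be 0%, and the anthropometry prompts are put into the EHR of one arm only, so an empty control arm is a realistic result. The model and effect measure in {20a} then produce no reportable estimate at the value the trial was planned on, while Table 2 tells the reader that the comparison has more than 99% power. The two sections describe different analyses of the same measure. The trial could reach its 50% target and still have to report a ratio of infinity, or replace the method after seeing the data.

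**Working it through.** **Inputs.** Control 0% and intervention 50% (Table 2). Seven clinics per arm ({16a}). 333 enrolled per clinic, 10% refusal and 10% loss to follow-up ({14}), giving 333 × 0.9 × 0.9 ≈ 270 analysed per clinic and 7 × 270 = 1,890 per arm. "a within-clinic correlation of 0.055" ({14}). Two-sided 5%. Deducting both losses and using equal clinic sizes are assumptions; the plan expects sizes to vary.

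**Step 1: the plan's own figure.** The design effect is 1 + 269 × 0.055 = 15.8. For a risk difference over c pairs, SE² = [p0(1−p0) + p1(1−p1)] × 15.8 / (270c).
- c = 7: SE = √(0.25 × 15.8 / 1,890) = 0.0457; 0.50/0.0457 = 10.9; power is essentially 100%.
- c = 5 (a conservative two-pair deduction): SE = √(0.25 × 15.8 / 1,350) = 0.0541; 0.50/0.0541 = 9.2; power again essentially 100%.
- Minimum detectable difference with p0 = 0: solve p² = (1.96 + 1.2816)² × p(1−p) × 15.8 / (270c). This gives 8.1 points for c = 7 and 10.9 for c = 5, against 10% stated.

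The >99% is reproduced, as a statement about an absolute difference.

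**Step 2: the risk ratio with no control events.** With 0 of 1,890, the likelihood keeps rising as the fitted control rate p0 falls, so there is no maximum at a finite ratio. Ignoring clustering, log RR = ln(0.5/p0) and SE² = (1−p0)/(1,890 p0) + 0.5/(1,890 × 0.5):

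| fitted p0 | log RR | SE | Wald z |
|---|---|---|---|
| 1e-4 | 8.5 | 2.3 | 3.7 |
| 1e-6 | 13.1 | 23 | 0.57 |
| 1e-8 | 17.7 | 230 | 0.08 |
| 1e-10 | 22.3 | 2,300 | 0.01 |

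The standard error grows faster than the estimate. At p0 = 1e-10, z stays near 0.01 for any uptake from 10% to 95%.

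**Step 3: simulation with clustering.** Beta-binomial clinics (ICC 0.055, 270 per clinic, 7 + 7), log-link binomial model with a clinic random intercept fitted by maximum likelihood, 100 runs per scenario. The paired t test uses clinic risk differences.

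| true control | uptake | runs with no control event | Wald rejects | likelihood-ratio rejects | paired t rejects |
|---|---|---|---|---|---|
| 0 | 10% | 100% | 0% | 100% | 97% |
| 0 | 50% | 100% | 0% | 100% | 100% |
| 0 | 80% | 100% | 0% | 100% | 100% |
| 0.05% | 50% | 85% | 15% | 100% | 100% |
| 0.1% | 50% | 79% | 21% | 100% | 100% |
| 0.5% | 50% | 23% | 77% | 100% | 100% |
| 2% | 50% | 0% | 100% | 99% | 100% |

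The Wald test fails in the same share of runs as have no control event. That share has a closed form: [B(a, b+270)/B(a, b)]⁷ with a = p0 × 17.18, b = (1−p0) × 17.18 and 17.18 = 0.945/0.055. At 0.05%, 0.1% and 0.5% it is 84%, 71% and 18%, implying Wald power near 16%, 29% and 82%. The simulated values agree within the error of 100 runs. The simulation left out the pair effect; adding it cannot make the estimate finite when every control count is zero.

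**Step 4: precision of the intervention arm.** At 50%, SE = 4.6 points; times the t quantile 2.447 (6 df) this is about ±11 points.

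**The case against.** Several counter-arguments have force.

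- **No Wald test is named.** Section {20a} promises a ratio with a 95% CI and does not say how the interval is built. A reader might infer that the mixed model can never detect the difference; the documents do not support that, since a likelihood-ratio test from the same model rejected in every run with an empty control arm. It rescues the p-value only: the ratio stays infinite, with no upper limit.
- **The 0% need not be structural.** The article describes prompts and does not say that the control EHR lacks a field. The next row of Table 2 plans 2% in control for 10-year CVD risk under the same unmodified EHR, and any rate below 0.5% prints as 0%. Complete failure therefore holds only if no control participant has a record; otherwise it is partial, and at 2% it is gone.
- **The row is named only in Table 2.** Table 1 has no waist/hip item; the nearest is the broader Adoption item on screening for other CVD risk factors using the EHR. That {20a} governs this row is a reasonable reading, but a reading.
- **Fallbacks for sparse data belong in the analysis plan.** True of a missing fallback. Here, though, the effect measure the article does state is undefined at the article's own planning value.
- **The >99% might be read as a wrong number, or the risk difference as a foregone result.** Neither follows. The power figure is right on its declared basis. A prompt is not a record, so whether staff act on it is a real question, and Table 2 openly gives a 10-point detectable difference, which fits the 97% rejection at 10% uptake.

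**Conclusion.** The point holds in limited form. At 0% in control, the risk ratio with 95% CI in {20a} cannot be reported for this row: there is no finite estimate or upper limit, and a Wald interval rejects in 0 of 100 runs whatever the uptake. At a control rate of 0.05% to 0.5%, simulated Wald power is about 15% to 77%. The >99% stands for the pair-matched absolute difference and should not be carried over to the ratio.

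This rests on an ICC of 0.055 also applying to this measure, beta-binomial variation between clinics, about 270 analysed per clinic, and {20a} covering this row. The near-zero figures are sensitive to the assumed clustering; the lack of a finite ratio with no control events is not. The consequence is confined to this Adoption measure and any other EHR-field outcome with an empty or almost empty control arm. It does not set the sample size and leaves both co-primary outcomes untouched.

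**What to change.** 1. In {20a}, state that for this endpoint, and for any EHR-field outcome with zero or near-zero control events, the effect measure is the risk difference from clinic-level proportions within pairs, with 95% CI, in place of the mixed-model risk ratio. This is the basis Table 2 already uses.
2. Report alongside it the intervention-arm proportion with a clinic-level 95% CI (7 clinics, 6 df) against the 50% target. If every control clinic is at zero, the two estimates and intervals coincide; they differ once any control record exists.
3. Keep the >99% in Table 2 and note that it refers to the risk-difference analysis.

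Cost: one or two sentences in {20a} and a table note, with no new data. The downside is that this row carries a different effect measure from the other binary outcomes.

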### Recruitment {15}

Strategies for achieving adequate participant enrolment to reach target sample size is to enroll sites in pairs, i.e., one controlled site will be enrolled with one intervention site simultaneously. Before enrolment, community/stakeholder engagement followed by pre-implementation surveys will be done for each site. Training of providers on protocol and EHR changes as well as hypertension management will be done at intervention sites. Participants will be mainly enrolled during their IDCC visit (HIV-related clinic visit). To scale up enrolment, participants will also be enrolled when they came for other HIV-related services at other departments such as laboratory and pharmacy.

## Assignment of interventions: allocation

### Sequence generation {16a}

Using the coin flip randomization method, 14 clinics will be randomized to a trial arm (*n* = 7 intervention, *n* = 7 control). Since patients are registered at one clinic only (and do not tend to visit more than one clinic), participants cross-over between intervention and control clinics is unlikely; hence, we do not expect contamination to become an issue.

### Concealment mechanism {16b}

IRB approval was first granted centrally for all potentially eligible sites. Then, facility assessment readiness and willingness to participate were done. Once a rolling list of 14 sites had been reached, a study launch site was done systematically as pairs (control and associated intervention sites). Ultimately, our approach allowed for allocation concealment until randomization and study activation team was ready to activate the site.

### Implementation {16c}

Our research assistants will enroll participants who will then be exposed to the implementation strategies by healthcare providers at their HIV clinic.

## Assignment of interventions: blinding

### Who will be blinded {17a}

There was no blinding, as this is not feasible because our trial is focused on strategies to improve HTN/CVD care in the intervention sites; thus, both providers and participants ought to be aware. It was also difficult to blind our analysts as our biostatisticians work closely with the clinical operations team to track and document variability across sites, and recommend continuous adaptations, and gain understanding of why interim site data is changing.

### Procedure for unblinding if needed {17b}

This is not applicable; there was no blinding.

## Data collection and management

### Plans for assessment and collection of outcomes {18a}

#### PLWH and HTN

Following informed consent, study data from participating PLWH will be collected at baseline and then at study visits at months 6, 12, 18, and 24 for the PLWH and their treatment partners. Socio-demographics, co-morbidities, medication intake, cardiovascular health data including a blood pressure assessment, and treatment partner sessions will be collected in the study electronic database.

#### Treatment partners

A survey will be adapted from previous work on HIV treatment partners [16] to measure delivery of support to PLWH and HTN including frequency, type, and other activities. The survey will be done monthly until the BP of the patient is controlled and then every 3 months.

#### Key partners

Key partner surveys and interviews will be conducted, 1–2 months pre-implementation and then between months 55 and 60 (post-implementation). The surveys and interviews will be designed using the Consolidated Framework for Implementation Research (CFIR) 1.0 [22, 23] framework to identify potential barriers to and facilitators of implementation along the 5 CFIR domains: (1) characteristics of individuals—PLWH, health care providers, and treatment partners, (2) process of implementation of InterCARE strategy package, (3) outer setting which includes household, social network, and community, (4) inner setting (the HIV clinic), and (5) intervention (HTN management) characteristics. The surveys will be administered in English, and interview guides are translated to Setswana (local language) so that the interviews could be done in English or Setswana as needed. All key partner surveys and interviews will be face-to-face (or by phone where meeting in person is difficult). Interviews sessions will be recorded using a digital audio recording device and transcribed.

### Plans to promote participant retention and complete follow-up {18b}

We will obtain patients’ and their treatment partners’ contact information (mobile phone number, addresses) and the contact information of someone who might know their whereabouts; we will also ask permission to track them through the clinic (e.g., to find them at appointments). We will use the EHR to create a list of patients with hypertension for tracking, to ensure they attain blood pressure control (just like we have done for patients experiencing virologic failure). Both the patient and their treatment partners will be called and reminded to attend scheduled study-related sessions and treatment partner sessions.

### Data management {19}

Collected data will be managed using the Research Electronic Data Capture (REDCap) tool hosted at the University of Botswana. REDCap [24, 25] is a secure, web-based software platform designed to support data capture for research studies, providing (1) an intuitive interface for validated data capture, (2) audit trails for tracking data manipulation and export procedures, (3) automated export procedures for seamless data downloads to common statistical packages, and (4) procedures for data integration and interoperability with external sources.

### Confidentiality {27}

Confidentiality will be maintained from consent to data destruction, covering participants, their data, and study records. Identifiable data will not be shared without written consent, except for monitoring by authorized entities like IRBs, sponsors, regulators, approved monitors, or the Botswana Ministry of Health.

### Plans for collection, laboratory evaluation, and storage of biological specimens for genetic or molecular analysis in this trial/future use {33}

This is not applicable; we will not collect any biological specimens.

## Statistical methods

### Statistical methods for primary and secondary outcomes {20a}

Primary analyses will be based on the intention-to-treat principle supported by per protocol analysis. The primary effectiveness outcome will be analyzed using a generalized linear mixed model (GLMM). The model will have a binomial distribution and log link function with the treatment (treatment vs control) as fixed effect, clusters, and pairs as random effects. From GLMM, the risk ratio with 95% confidence intervals (CI) will be calculated.

In addition, adjusted GLMM model analysis will be performed with covariates measured at baseline being added into the above GLMM model. The following variables will be considered in the covariate adjusted analysis: age, sex, education, level of income, waist to hip ratios (or body mass index (BMI)), physical activity (estimated number of minutes walked per week), smoking, and alcohol consumption.

Analysis of secondary binary outcomes will be analyzed similarly as the analysis of primary outcome using GLMM models. Analysis of secondary continuous outcomes will be performed using GLMM models with normal distribution and identity link function. The models will have the treatment as fixed effect, cluster, and pair as random effects. The mean differences with 95%CIs between treatment and control will be derived from the GLMM model.

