### Eligibility criteria {10}

Patients are eligible if they (1) are aged between 20 and 75 years old, (2) have documented HIV infection and are on ART, (3) have a confirmed diagnosis of HTN or elevated systolic blood pressure (SBP) ≥ 140 or diastolic blood pression (DBP) ≥ 90 mmHg (or SBP ≥ 130 or DBP 80 mmHg if they have diabetes mellitus or chronic kidney disease), and (4) are a registered client at the selected clinics. PLWH are not eligible if they are documented as having a diagnosis of dementia in clinic records or if they are unable or unwilling to provide informed consent. PLWH and HTN will be selected for enrolment using a purposive random sampling method by trained research assistants at each site.

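### The covariate list leaves out baseline blood pressure or control status, the baseline value of the primary outcome, which costs precision and robustness with only 7 clinics per arm

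*Protocol article*

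**What the plan says.** All of this is in the protocol article.

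- **Primary model** (Statistical methods for primary and secondary outcomes {20a}): a log-link binomial GLMM "with the treatment (treatment vs control) as fixed effect, clusters, and pairs as random effects". It has no baseline term.
- **Adjusted model** (same section): "The following variables will be considered in the covariate adjusted analysis: age, sex, education, level of income, waist to hip ratios", with BMI as an alternative to the last item. The list ends with "physical activity (estimated number of minutes walked per week), smoking, and alcohol consumption". It is a closed list, and no blood pressure variable is in it.
- **Continuous secondary outcomes** (same section): a normal, identity-link model, again with treatment as the only fixed effect. Table 1 defines the blood pressure outcome as a difference between the baseline, 12-month and 24-month visits.
- **Data planned** (Plans for assessment and collection of outcomes {18a}): "study data from participating PLWH will be collected at baseline and then at study visits at months 6, 12, 18, and 24", and these data contain "cardiovascular health data including a blood pressure assessment".
- **Who is enrolled** (Eligibility criteria {10}): patients qualify if they "have a confirmed diagnosis of HTN or elevated systolic blood pressure" or diastolic pressure above a threshold. Selection is described as "PLWH and HTN will be selected for enrolment using a purposive random sampling method by trained research assistants at each site".
- **Blinding** ({17a}): "There was no blinding, as this is not feasible". This covers the analysts too.
- **Matching** (Study setting {9}): firm matching is on staffing and patient numbers. Other factors are optional.

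**The concern.** The baseline value of an outcome is usually among its best predictors. The article does not say so; this is a statistical judgement. Here it is planned data, yet the list spends its terms on weaker candidates such as minutes walked per week.

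Two features make baseline control likely to vary between clinics. A patient with a confirmed diagnosis may already be controlled at entry, whereas one who enters on an elevated reading is not controlled on that reading, so a clinic's mix of entry routes shifts its baseline control. The firm matching factors do not address this mix.

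The number of randomised units is also small. With 14 clinics, large enrolment per clinic does little to even out clinic-level differences. Age, sex or smoking cannot be relied on to stand in for baseline blood pressure. At stake are the width of the interval around the risk ratio and how easily a reader can trust it if the arms turn out to start from different levels of control.

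**Working it through.** **Inputs from the article.** 7 clinics per arm in pairs ({9}, {16a}). ICC 0.055, about 333 per clinic, 10% loss to follow-up (so about 300 evaluable) and a two-sided 95% interval (Sample size {14}). Control 19% under standard care against a 64% target, with power above 99% and a minimum detectable difference of 21% (Table 2). The abstract also gives 19% for current control. Using 19% as the baseline level among enrolled patients is an assumption.

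**Step 1: the plan's own figures.** For a pair-matched design, k pairs = 2 + (1.96 + z_power)² × [p0(1−p0) + p1(1−p1)] × [1 + (m−1)ICC]/m ÷ (p1−p0)². Seven pairs leave 5 effective pairs. With m = 333, [1 + 332 × 0.055]/333 = 0.0578.

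- 19% vs 64%: power above 99.9%, minimum detectable difference 21.9 points (stated: above 99%, 21%).
- 57% vs 80%: power 91.9%, minimum detectable difference 22.3 points (stated: 93%, 22%).

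Table 2 is reproduced closely, so its ICC and clinic size are used below.

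**Step 2: chance imbalance at baseline, ignoring matching.** SD of the arm difference = √{2p(1−p)[ICC + (1−ICC)/m]/7}. With p = 0.19 and m = 333:

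√{2 × 0.1539 × (0.055 + 0.945/333)/7} = √0.00254 = 0.050, or 5.0 points.

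- P(gap above 5 points): about 32%.
- P(gap above 10 points): about 5%.

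The between-clinic SD is √(0.055 × 0.1539) = 9.2 points. About 95% of the variance of a clinic mean lies between clinics, so more patients per clinic would not help.

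**Step 3: precision gained by adjusting.** The article gives no clinic-level correlation r between baseline and follow-up control, so a range is assumed. The variance is multiplied by (1 − r²) and one degree of freedom is spent (6 to 5). At 19% vs 64%, with m = 300, the unadjusted SE is √{(0.1539 + 0.2304) × 17.445/(300 × 7)} = 5.65 points.

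| r (assumed) | SE, points | t-based 95% half-width, points | Change in width |
|---|---|---|---|
| unadjusted | 5.65 | 13.8 | – |
| 0.3 | 5.39 | 13.9 | none |
| 0.5 | 4.89 | 12.6 | about 9% narrower |
| 0.7 | 4.04 | 10.4 | about 25% narrower |

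Power at the 64% target exceeds 99% in every row. For 57% vs 80%, the Step 1 formula with m = 300 and the same variance reduction gives 91.8% unadjusted and 94.0%, 97.2% and 99.7% at r = 0.3, 0.5 and 0.7. That formula does not charge the lost degree of freedom, so these three are slightly favourable.

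**The case against.** - **Randomisation already covers chance imbalance.** This stands. Chance differences between clinics are carried into the standard error by the cluster and pair effects. Step 2 shows how often a visible gap would arise; it does not show a wrong primary result.
- **Power is ample.** This also stands for the 45-point target. A reader might infer that the trial is underpowered without the adjustment, and the figures do not support that.
- **Selective enrolment.** A reader might infer that unblinded research assistants enrolled different patients in the two arms. Sites were opened in pairs with provider training at intervention sites, so the arm could be known when patients were recruited, and randomising clinics does not protect against that. But nothing in the article shows that it happened. It is a risk that could add to chance imbalance.
- **The continuous outcomes ignore baseline.** That reading is too strong. Table 1 defines a difference from baseline, so the baseline value is inside the outcome. What is missing is its use as a covariate. Some patients enter on an elevated reading, so regression to the mean can distort a change comparison when the arms start at different levels.
- **The magnitude rests on assumptions.** Agreed. Effective matching would shrink both the imbalance and the gain, the correlations are assumed, and at 0.3 nothing is gained in width.
- **It can be left to the analysis plan.** Only in part. The variables are to be considered rather than fixed as final, and a separate plan is mentioned. But the article writes out a complete list, and that list omits this variable.
- **Changing the primary model now is delicate.** This stands. Recruitment ended in September 2023, and the analysts are unblinded and follow interim site data. The fix has to allow for it.

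**Conclusion.** The point holds as a weakness in efficiency and robustness. It is not bias by design and it is not inadequate power. The models as written omit the baseline value of the primary outcome, which the trial plans to collect. Planned collection does not prove that the value is complete for everyone.

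The imbalance figures rest on the article's ICC and 19% control, with no credit for matching. The narrowing of 9% to 25% rests on assumed correlations of 0.5 to 0.7 and vanishes at about 0.3. Even there, adjustment would answer the question that an observed baseline gap would raise. The change should be made, but the trial's main comparison does not depend on it.

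**What to change.** Before the outcome analysis:

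1. Add **one** baseline blood pressure term to the adjusted GLMM, and preferably to the primary model: either baseline control status, defined by the same rule as the outcome, or baseline SBP. Several overlapping terms are not needed and would strain a log-binomial mixed model.
2. Report the unadjusted result alongside.
3. Name a fallback in case the log-binomial model does not converge, for example a two-stage analysis on clinic-level residuals.
4. For the SBP and DBP differences at 12 and 24 months, add the baseline value as a covariate (ANCOVA).

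**Cost.** No new data collection is planned for this. It costs one degree of freedom at clinic level (6 to 5 in the calculation above), which cancels the gain if the correlation is about 0.3, and it may cause convergence problems. Because the analysts are unblinded, the change needs a dated, documented justification before outcomes are analysed, so that it cannot be taken for a response to an observed imbalance. If changing the primary model at this stage is judged too exposed, putting the term in the planned adjusted analysis is the minimum.
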